## 9.3 EXPLORATORY VARIABLES (wherever possible)

- C-reactive protein,
- Soluble GPVI (sGPVI),
- D-Dimers,
- Prothrombin time,
- Troponine T,
- IL-6
- Procalcitonin,
- Ferritin
- Lactate dehydrogenase.

## 9.4 OTHER BIOLOGICAL

### 9.4.1 Pharmacokinetics (PK)

Glenzocimab plasma concentration will be assayed as described below.

At Days 1, 2 and 3 the following 3 blood samples should be taken:

1. Baseline at the beginning of each treatment period,
2. 3 hrs after the beginning of the first study drug administration,
3. 3 hrs after the end of the study drug administration,

On Day 4, a last sample will take place 24hrs (+/-1hr) after initiation of the last infusion performed at Day 3.

Determination of glenzocimab is done in human platelet-poor plasma. Isolation of glenzocimab is performed by immunocapture, reduction, alkylation, and digestion followed by solid phase

extraction. After evaporation, the reconstituted extracts are analyzed using high performance liquid chromatography-tandem mass spectrometry (LC-MS/MS). The method has been validated at QPS (NL), that will perform the assays for the present study too.

PK results WILL NOT be forwarded to investigators during the course of the study, with exception of an emergency procedure for the management of an SAE if deemed appropriate, this in order to keep the study blind.

#### **9.4.2 Immunogenicity-ADA**

Dosing with glenzocimab may lead to the development of glenzocimab-specific antibodies. Presence of anti-glenzocimab antibodies (ADA) will be assessed at the last visit (D20, end of study), as well as in case of immunologic adverse reactions. A validated assay will be used to assess the presence of anti-glenzocimab antibodies in human serum samples. The anti-glenzocimab antibody assay runs on the MSD ECL platform. The samples are incubated with biotinylated glenzocimab (ACT017-Bio) and SULFO-tag labeled ACT017 (ACT017-SULFO). The samples are then transferred to a standard Streptavidin Gold Multi-array 96 well plate. The ACT017-Bio in the formed complex binds to the streptavidin on the plate and detection is performed via the ACT017-SULFO in a Sector Imager S 600 after applying a current to the plate. The intensity of the emitted light is measured.

This method has been validated at QPS (NL) that will performed the assays for the present study too.

Assays should be performed in totality after the end of all patients clinical administration. However, should an SAE be suspected to be of immunologic origin, an emergency assay should be performed immediately upon notification.

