## 4.2 STUDY DURATION FOR THE PATIENT

For each given patient, schedule will include:

- A screening assessment upon admission to ensure of diagnosis and inclusion criteria
- At Day 1:
  - a baseline visit followed by a randomization procedure, initiation of first infusion,
  - a post-infusion evaluation at 3 hrs (+/-1hr) after the end of administration.
- At Day 2:
  - Initiation of second infusion (pending results of prior evaluation)
  - A post-infusion evaluation at 3 hrs (+/-1hr) after the end of second administration if a second administration takes place.
- At Day 3:
  - Initiation of third infusion (pending results of prior evaluation)
  - A post-infusion evaluation at 3 hrs (+/-1hr) after the end of third first administration if a third administration takes place.
- At day 4: a follow-up evaluation at 96 hrs (+/- 3 hrs), post beginning of first administration (primary end-point recording).
- At day 5: a follow-up evaluation at 120 hrs (+/-3 hrs), post beginning of first administration.
- In case, the administration is not repeated, post-infusion evaluation at 3hrs at Day 2 and Day 3, Day 4 (96 hrs), Day 5 (120 hrs) visits should take place anyway.
- A follow-up visit at Days 7 (+/-1 day), 14 (+/- 2 days) and 20 (+/-2 days),

- A 40-day (+/-3 days) post-treatment final evaluation, (End-Of- Study visit).

Additional follow-up visits, or phone calls may be required on a need basis notably in case of emerging or prolonged adverse events. Remote visits utilizing specific devices can be undertaken if it is not desirable that the patient, if discharged comes back to the institution.

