#### **7.12 DAY-40: END OF STUDY VISIT**

The following examinations will be performed:

- Clinical evaluation;
- Vital signs (BP, Pulse);
- RT-PCR test;
- Viral load test;
- 12-lead ECG;

- Respiratory distress parameters:
  - Respiratory Rate (RR),
  - Oxygen saturation (SpO2),
  - PaO2/FiO2;
- NEWS-2 and/or WHO scales;
- Urine or serum (β-hCG) pregnancy test;
- Local blood sample test;
- Blood sample for Anti-glenzocimab antibodies (ADA) assessments will be collected and sent to the central laboratory;
- Concomitant medication;
- Recording of adverse events according to NCI-CTCAE (version 5.0) and SAEs.

For the 40-day evaluation, a window of  $\pm 3$  days is allowed.

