### 7.13.2 Pharmacokinetics, soluble GPVI and Immunogenicity Assessments

It is of utmost importance to collect all blood samples at the specified times and according to the specifications.

Samples missed or lost, for any reason, should be recorded. Actual date and times of blood collection must be recorded in the eCRF. The date and the time of drug administration should also be precisely recorded.

PK will be assessed and sampling times for blood collection can be found in the study flow chart (see [Section 7.1](#)).

Plasma samples for PK, soluble GPVI and immunogenicity assessments will be analyzed by a Central Laboratory and those samples should be transferred according to the detailed procedure described in the Central laboratory instruction manual.

| Visit                    | Time                                 | Sample nr
PK | Sample nr
ADA | Sample nr
sGPVI |
|--------------------------|--------------------------------------|-----------------|------------------|--------------------|
| Visit 2 Day 2 (V2D2)     | Baseline                             | 201             | 211              | 221                |
|                          | 3hrs after start of infusion         | 202             |                  |                    |
|                          | 3hrs after end of infusion           | 203             |                  |                    |
| Visit 3 Day 3 (V3D3)     | 24hrs after 1 st infusion | 301             |                  |                    |
|                          | 3hrs after start of infusion         | 302             |                  |                    |
|                          | 3hrs after end of infusion           | 303             |                  |                    |
| Visit 4 Day 4 (V4D4)     | 24hrs after 2 nd infusion | 401             |                  |                    |
|                          | 3hrs after start of infusion         | 402             |                  |                    |
|                          | 3hrs after end of infusion           | 403             |                  |                    |
| Visit 5 Day 5 (V5D5)     | 24hrs after 3 rd infusion | 501             |                  |                    |
|                          | 96hrs evaluation                     |                 |                  | 521                |

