| Visit 10 Day 40 (V10D40) | EOS                                  |                 | 1011             |                    |

Table 1: laboratory assessment and sample numbers

PK analyses will be done at QPS (see [Section 9.4.1](#)).

Potential presence of ADA will be determined at QPS in all patients enrolled and sampling times for blood collection can be found in the study flow chart (see [Section 7.1](#)). In case the patient presents clinical symptoms suggesting the potential presence of ADA, a blood sample may be collected outside of the scheduled visits as unscheduled ADA assessment see [Section 9.4.2](#)).

Sample handling, storage, and shipping conditions will be described in a specific manual intended for the investigating team.

QPS should be provided in due time and with a procedure that complies with blinding conditions with the list of tubes (both for PK and ADA) that stem from patients having received the active IMP.

To avoid any unintended unblinding, all the results related to PK and ADA won't be shared with either the sites staff, the Sponsor nor the CRO staff involved in the study management before the database lock.

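### Section 9.4.2 gives the wrong day and a conflicting matrix for the anti-drug-antibody sample, and the laboratory is told which antibody tubes come from the active arm

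*Protocol*

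**What the plan says.** Three parts of the Protocol govern the ADA sample.

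- **Day.** Section 9.4.2: "Presence of anti-glenzocimab antibodies (ADA) will be assessed at the last visit (D20, end of study), as well as in case of immunologic adverse reactions". It mentions no pre-dose sample. Section 4.2 defines the end of study differently: "A 40-day (+/-3 days) post-treatment final evaluation, (End-Of- Study visit"). Section 7.12 (Day 40) includes the item "Blood sample for Anti-glenzocimab antibodies (ADA) assessments will be collected and sent to the central laboratory", and section 7.3 has the same item at baseline.
- **Matrix.** Section 9.4.2: "A validated assay will be used to assess the presence of anti-glenzocimab antibodies in human serum samples". Section 7.13.2: "Plasma samples for PK, soluble GPVI and immunogenicity assessments will be analyzed by a Central Laboratory".
- **Who is tested.** Section 7.13.2: "Potential presence of ADA will be determined at QPS in all patients enrolled". A little further on, the same section has the laboratory receive the "list of tubes (both for PK and ADA) that stem from patients having received the active IMP". It gives no purpose for the list.

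**The concern.** The section devoted to immunogenicity disagrees with the visit schedule about when the tube is drawn and with the sampling section about what is in it. A site or laboratory that follows one section on the matrix breaches the other. Serum and plasma need different collection tubes, so the error cannot be repaired after the draw. Separately, the assayer is told which ADA tubes come from treated patients.

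The ADA result matters here beyond routine safety reporting. The earlier human exposure described in the Protocol is single-infusion (sections 2.2.4 and 2.2.7), and so are the toxicology studies (section 2.2.2). Section 2.2.7 cites a low predicted immunogenicity among its grounds for needing no further repeat-dose studies. Section 11.5.2 commits to reporting ADA frequency and severity. This trial therefore gives the first ADA data after repeated infusions, in a small arm, where each positive has to be interpreted individually.

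**Working it through.** No figure in the Protocol depends on this point, so there is none to reproduce. The check is a comparison of sections, followed by a calculation for scale only.

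**Day**

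- 9.4.2: Day 20, labelled the last visit and end of study; no baseline sample named.
- 7.3: ADA sample before randomization.
- 7.11 (Day 20 visit): no ADA sample listed.
- 7.12 (Day 40, end of study): ADA sample listed.
- 7.13.2, Table 1: ADA tube 211 at baseline and tube 1011 at Day 40. There is no tube number for Day 20.
- 7.1 flowchart: the ADA row is broken in the text available, so I did not rely on it.

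Every other legible place agrees on baseline and Day 40. Section 9.4.2 stands alone.

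**Matrix**

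- 9.4.2: the ADA assay is described for serum.
- 7.13.2: one sentence covers PK, soluble GPVI and immunogenicity samples and calls them all plasma.
- Elsewhere the Protocol names the matrix with care: platelet-poor plasma for PK (9.4.1) and citrated platelet-poor plasma for soluble GPVI (7.13.1). The word serum in 9.4.2 is therefore hard to dismiss as loose wording.
- No validation of the ADA assay in plasma is cited.

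**Who is tested**

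- 7.13.2 says all enrolled patients.
- 7.13.2 also supplies the list of active-arm tubes, for PK and ADA together.
- For PK the list has an evident use, since placebo tubes hold no drug to measure. For ADA it has none if both arms are assayed, because a placebo tube is an informative negative control.
- Nothing states that unlisted tubes go untested.

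**Scale**

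Inputs: a predicted ADA response of 2.00% (+/-5%) from section 2.2.7; 30 evaluable patients per arm from section 11.4; 68/2 = 34 randomized per arm. I read +/-5% as percentage points, which is an assumption. The upper end is then 2% + 5% = 7%, and the lower end is truncated at 0.

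Expected positives = n × p, and P(at least one) = 1 − (1 − p)^n.

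- n = 30, p = 0.02: 30 × 0.02 = 0.6; 1 − 0.98^30 = 45.5%.
- n = 34, p = 0.02: 34 × 0.02 = 0.68; 1 − 0.98^34 = 49.7%.
- n = 30, p = 0.07: 30 × 0.07 = 2.1; 1 − 0.93^30 = 88.7%.
- n = 34, p = 0.07: 34 × 0.07 = 2.38; 1 − 0.93^34 = 91.5%.

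Exact (Clopper-Pearson) 95% intervals: 0 of 30 gives 0 to 11.6%; 1 of 30 gives 0.1 to 17.2%.

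The active arm will probably yield none, one or two positives. What one positive means depends on the patient's own pre-dose tube and on how often masked placebo tubes also read positive.

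**The case against.** The strongest reply is that this is mostly drafting. A site working from its visit list and tube numbers would draw at baseline and Day 40 whatever 9.4.2 says. Section 9.4.2 itself ties the sample to the end of study, which is Day 40 everywhere else. The plasma statement is one umbrella sentence, and sample handling is left to a laboratory manual that is not shown. Section 7.13.2 says plainly that all enrolled patients are tested, that the list is supplied under a procedure respecting the blind, and that results are withheld from sites, sponsor and CRO study staff until database lock. Section 9.4.2 defers the assays until all patients have been dosed, emergencies aside. ADA is not among the objectives in section 3 or the endpoints in sections 8 and 9.1 to 9.3.

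Much of this stands, and it rules out several stronger readings:

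- A reader might infer that antibodies get only 20 − 3 = 17 days after the third infusion to appear, instead of 40 − 3 = 37. The schedule never draws ADA at Day 20, so that loss does not arise.
- A reader might infer that only the active arm is tested. The text does not say so. The two statements are in tension but do not contradict each other.
- A reader might infer that false positives cannot be recognised. Placebo tubes are collected, and each patient has a pre-dose tube.
- A reader might infer that a serum-only assay will be run on plasma. The Protocol does not show which tube is drawn, or whether plasma has also been validated.
- One patient is 1/34 = 2.9 or 1/30 = 3.3 percentage points of the arm. That follows from the arm size and does not measure harm from these passages.

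Two things survive. Neither the serum/plasma conflict nor the day conflict can be resolved from 9.4.2 and 7.13.2 as written. And the blinding safeguards cover sites, sponsor and CRO, but not the laboratory, which is the party that receives the list.

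**Conclusion.** The point holds as two direct inconsistencies and one avoidable ambiguity.

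1. Day 20 in 9.4.2 is an isolated error, as is its silence on the baseline sample. The consequence is small, because the schedule and Table 1 agree with each other.
2. Serum against plasma is the most consequential part. If the assay is validated in serum only and plasma is drawn, its cut-points would be used outside their validation. That is conditional: the Protocol neither cites nor excludes a plasma validation.
3. The list reveals treatment arm to the ADA assayer without need, and leaves open whether placebo tubes are assayed despite the statement that all patients are tested.

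A reader might go further and conclude that the ADA rate will be uninterpretable. The documents do not support that: baseline and Day 40 tubes are planned in both arms, and testing of all enrolled patients is stated. With 0.6 to 0.7 positives expected at the predicted 2%, or 2.1 to 2.4 at 7% under the percentage-point reading, the supportable conclusion is narrower. Interpreting any single positive needs the pre-dose tube, a matrix suited to the assay, and placebo tubes read without knowledge of arm. The change should be made, but nothing in the primary efficacy analysis depends on it.

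**What to change.** - In 9.4.2, replace the Day 20 reference with baseline and Day 40 (end of study), matching 7.3, 7.12 and Table 1. Keep the additional sample after an immunologic reaction.
- Make 9.4.2 and 7.13.2 name one matrix that matches the validated assay: either specify a serum tube for ADA, or cite documented validation in the plasma actually collected. Carry the same wording into the laboratory manual.
- In 7.13.2, limit the active-tube list to PK. State that the baseline and Day 40 ADA tubes of both arms are assayed by staff masked to arm.

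The cost is Protocol and laboratory-manual wording, a different ADA tube if serum is chosen, and any additional assays on tubes from about 34 placebo patients (68/2). Sections 7.3 and 7.12 already collect those samples, so no visit or patient is added.

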### **9.5 DEFINITIONS**

#### **9.5.1 Adverse Event (AE)**

An adverse event is any untoward medical occurrence in a patient or clinical trial subject administered a medicinal product and which does not necessarily have a causal relationship with this treatment. An adverse event can therefore be any unfavorable and unintended sign (including an abnormal result of an investigation), symptom or disease.

In clinical studies, an AE can include an undesirable medical condition occurring at any time, including run-in or wash-out periods, even if no experimental treatment has been administered.

#### **9.5.2 Treatment Emergent Adverse Event (TEAE)**

Treatment emergent adverse events are defined as adverse events which occur during or within the 30 days after the administration of the first dose of the investigational medicinal product (IMP) or if present before the first administration of IMP, worsens on study treatment.

#### **9.5.3 Adverse Drug Reaction (ADR)**

An adverse drug reaction is any untoward and unintended response to a medicinal product related to any dose administered.

#### **9.5.4 Unexpected Adverse Drug Reaction (ADR)**

Any adverse drug reaction the nature, severity or outcome of which is not described in the applicable product information.

In this study, the reference document to be used to evaluate the unexpectedness of the adverse drug reactions is section “summary of data and guidance for the investigator” in the Investigator's Brochure (most recent version) for glenzocimab.

### **9.5.5 Adverse Event of Special Interest (AESI)**

Bleeding-related adverse events, thrombotic events, and hypersensitivity events will be subject to a specific analysis.

### **9.5.6 Laboratory Test Abnormalities**

Abnormal laboratory test value should only be reported as an AE if any of the following apply:

- it is accompanied by clinical symptoms or is considered as medically significant by the investigator;
- it results in a change in study treatment schedule of administration (for example, delay in administration, temporary or permanent discontinuation);
- it requires a therapeutic intervention or a change in concomitant treatments.

## **9.6 REPORTING OF ADVERSE EVENTS**

All AEs (related and unrelated to the IMP, expected and unexpected) occurring in the course of the study, from the signature of the study informed consent form and until 30 days after the last dose of the study drug, are to be reported by the investigator.

The Investigator should specify the onset date (with the time to onset since the last IMP infusion (if less than 24 hrs), end date, severity, seriousness, action taken with respect to Investigational Product (glenzocimab or placebo), corrective treatment/therapy given, outcome and his/her opinion as to whether there is a reasonable possibility that the Adverse Event was caused by the (glenzocimab or placebo).

During the study follow-up period (beyond 30 days after the last dose of the study drug) all AEs related to the IMP (glenzocimab or placebo) will be reported.

All AEs reported spontaneously by the patient, elicited as a result of general questioning or observed by the investigator, will be recorded on the AE page(s) of the eCRF. AEs already recorded and described as being "ongoing" must be reviewed at each subsequent evaluation.

For all AEs, the investigator must search and obtain the necessary information to determine the outcome of the AE, whether it corresponds to the definition of a DLT and to assess whether it meets one of the criteria for classification as a serious adverse event (SAE) requiring an immediate notification to the PV Department of AIXIAL.

Any AE considered as related to the IMP (glenzocimab or placebo), will be followed until resolution or stabilization.

### **9.6.1 Intensity of AE**

AEs will be documented and graded according to the NCI-CTCAE version 5.0.

If, for a given AE, the NCI-CTCAE scale is not applicable, the following equivalences will be applied:

- NCI-CTCAE grade 1 corresponds to a mild intensity;
- NCI-CTCAE grade 2 corresponds to a moderate intensity;

- NCI-CTCAE grade 3 corresponds to a severe intensity or a disabling event;
- NCI-CTCAE grade 4 corresponds to a life-threatening event with urgent intervention indicated;
- NCI-CTCAE grade 5 corresponds to death (related to the AE).

### 9.6.2 Causality

The relationship of an AE to the IMP (glenzocimab or placebo) will be classified according to the following:

**Related:** an event is considered as related when a causal relationship between the event and the study drug can reasonably be suspected. Reports include good reasons and sufficient information (e.g. plausible time sequence, dose-response relationship, pharmacology) to assume a causal relationship with the study drug in the sense that it is plausible, conceivable or likely.

**Not related:** an event is considered as not related when a causal relationship between the event and the study drug cannot reasonably be suspected. Reports include good reasons and sufficient information (e.g. implausible time sequence and/or attributable to concomitant disease or other drugs) to rule out a causal relationship with the study drug.

## 9.7 SERIOUS ADVERSE EVENT

### 9.7.1 Definitions

#### Serious Adverse Event (SAE)

Any harmful clinical manifestation that, at any dose, fulfills at least one of the following criteria:

- is fatal (results in death; NOTE : death is an outcome, not an event);
- is life-threatening (NOTE: a "life-threatening event" refers to an event in which the patient was at risk of death at the time of the event; it does not refer to an event which could hypothetically might have caused a death if it were more severe);
- requires hospitalization or prolongation of existing hospitalization;
- results in persistent or significant disability or incapacity\*;
- is defined as a congenital anomaly or a birth defect;
- is a medically significant event.

\*The terms "disability" and "incapacity" mean any temporary or permanent physical or mental disability clinically significant which affects the physical activity and/or quality of life of the patient.

Is considered medically significant any clinical event or laboratory results considered as serious by the investigator and not corresponding to the seriousness criteria defined above. It may pose a risk to the patient and may require a medical intervention to prevent an outcome corresponding to one of the previously mentioned seriousness criteria (for example, an overdose, a second cancer, pregnancy or any new event which is susceptible to affect the safety of the patients may be considered as medically significant).

In this study, all adverse events of grade 4 will be notified as SAE including laboratory test abnormalities.

